## Abstract

The most common symptoms of post-COVID-19 condition in children are fatigue, shortness of breath, exercise intolerance, and weakness. The post-COVID-19 condition in children can be very debilitating and lead to prolonged school absences, high morbidity, and limitations in daily functioning. The aim of this research project is to determine the effectiveness of land-based and water-based exercise interventions on exercise capacity, fatigue, health-related quality of life, and pulmonary function in children with post-COVID-19 condition. This study is a prospective randomized controlled study with pre- and post-intervention assessment. Participants will be recruited from Warsaw’s primary schools and primary healthcare units according to the inclusion criteria: (i) symptoms of post-COVID-19 condition lasting more than one month following initial COVID-19 infection confirmed by the diagnosis by general practitioner (including obligatory fatigue and shortness of breath/respiratory problems); (ii) age 10–12 years old. Participants meeting the inclusion criteria will be randomized to one of three groups: water-based exercise, land-based exercise, or control (no exercise). We hope this study will provide guidance for long-COVID-19 rehabilitation in children.

## 1. Introduction

During the early stages of the COVID-19 pandemic, fatality was a major concern and area of intense investigation and intervention; however, this has now progressed to recognition of the physical and psychosocial post-acute consequences of COVID-19, called post-COVID-19 condition [1]. Post-COVID-19 condition is defined as occurring at least four weeks after the onset of COVID-19, with symptoms that last for at least two months and cannot be explained by an alternative diagnosis. Post-COVID-19 condition is a frequently occurring condition in children [2,3]. The most common symptoms of post-COVID-19 condition in children are fatigue, shortness of breath, exercise intolerance, weakness, muscle and joint pain, headache, insomnia, respiratory problems, and palpitations [4]. In a recent study of children post-COVID-19 infection, almost half presented with at least one symptom of post-COVID-19 condition over 60 days after initial infection [4]. Older age, muscle pain on hospital admission, and intensive care unit admission are significantly associated with experiencing post-COVID-19 condition in children [2]. The post-COVID-19 condition in children can be very debilitating and lead to prolonged school absences, high morbidity, and limitations in daily functioning [5,6]. Although children generally present with mild, acute COVID-19, they are at risk of prolonged organ damage, similar to what has been identified in adults [7]. It is important that long-term sequelae in children are not dismissed as psychological problems and to provide them with comprehensive diagnostic assessments, care, and support [8]. The basic biological mechanisms responsible for these debilitating symptoms are still unclear [9]. The COVID-19 pandemic profoundly affected young children’s development through loss of time in education, isolation, an increase in poverty and food insecurity, loss of caregivers, and heightened stress [2]. Further, there is also increasing evidence that restrictive measures aimed at limiting the pandemic had a significant impact on children’s mental health [4].

Rehabilitation after COVID-19 has the goal of improving respiratory symptoms, preserving function, and reducing complications and disability, and has a positive effect on the psychological sphere, reducing anxiety and depression [10]. A recent review highlighted the need to consider community-based pulmonary rehabilitation programs for COVID-19 survivors with compromised lung function [11]. People experiencing post-COVID-19 condition need support to manage their symptoms, especially fatigue, while also helping them safely pursue the potential benefits of exercise [12]. Organizational and service delivery issues have also arisen during the COVID-19 epidemic, which has altered face-to-face visits, with consultations being mostly in the form of online consultations [13]. Virtual group-based consultations may be a challenge for children. Interaction and non-verbal communication in the relationship between a young patient and their health professional are very important [14].

The range, severity, frequency, and duration of symptoms associated with post-COVID-19 condition in children present significant challenges for the precise recommendations for rehabilitation exercise training [12]. Guidelines provided by the American Academy of Pediatrics to assist in the management of return to sport and physical activity for children recovering from COVID-19 illness recommend that children who have asymptomatic disease or a mild form of the disease need to be screened by their primary care providers before returning to play. All children who have had COVID-19 should be asked about chest pain, shortness of breath, palpitations, or fainting [15]. A minimum of ten days of rest after the disease, including seven days without symptoms, and no cardiorespiratory symptoms when performing normal activities of daily living are advised [16].

The aquatic environment offers an opportunity to support and positively influence exercise in children. In children with respiratory conditions, the hydrostatic pressure provided by water improves the efficiency of the cardiorespiratory system [17]. Aquatic exercises also improve pulmonary function in children with obesity [18] and reduce the level of fatigue and improve the quality of life in children with juvenile dermatomyositis [19]. Specific breathing programs in water can improve lung function in adolescents with scoliosis [20]. In relation to the safety of the aquatic environment in the COVID-19 pandemic, research has demonstrated that chlorinated water reduces the SARS-CoV-2 infectious titer by at least three orders of magnitude [21]. Land-based exercise interventions are also effective in children with respiratory conditions. Children with asthma perceived that their fitness and asthma had improved and reported an increased health-related quality of life after six weeks of active play exercise intervention [22]. Eight weeks of regular submaximal exercise had beneficial effects on the quality of life and exercise capacity in children with asthma [23].

COVID-19 can have a long-term impact in children, and there is a need to implement measures to reduce the impact of post-COVID-19 condition on a child’s health and to ensure children receive appropriate therapeutic interventions. In particular, greater clarity and tailoring of exercise-related advice for children with post-COVID-19 condition and improved support to resume activities important to individual well-being is warranted. To the best of our knowledge, there are no studies describing exercise programs for children with post-COVID-19 condition.

### Objectives

The primary aim of this research project is to determine the effectiveness of land-based and water-based exercise interventions on exercise capacity and fatigue in children with post-COVID-19 condition.

The secondary aims are to determine the effectiveness of land-based and water-based exercise on health-related quality of life and pulmonary function in children with post-COVID-19 condition, and to compare outcomes to norms for healthy children.

## 2. Materials and Methods

This study is a prospective randomized controlled study with pre- and post-intervention assessment. The protocol was developed in accordance with the guidelines and checklists for Standard Protocol Items: Recommendations for Interventional Trials (SPIRIT) [24]. Results will be reported as stated in the Consolidated Standards of Reporting Trials (CONSORT) statement [25]. The study is being conducted at the Faculty of Rehabilitation, Jozef Pilsudski University of Physical Education in Warsaw (AWF Warsaw), Poland. The study has been registered on clinicaltrials.org (NCT05216549; 31 January 2022) and is in compliance with the latest version of the Helsinki Declaration [26]. The study was approved by the Ethics Committee of the AWF Warsaw. Written consent for participation will be expressed by the legal guardians of the children.

### 2.1. Study Population

Participants will be recruited from Warsaw’s primary schools and primary health-care units according to the inclusion criteria: (i) symptoms of post-COVID-19 condition lasting more than one month following initial COVID-19 infection confirmed by the diagnosis by general practitioner (including obligatory fatigue and shortness of breath/respiratory problems); (ii) age 10–12 years old. As it has been suggested that a positive COVID-19 test is not required for a diagnosis of post-COVID-19 condition [27], there will be an optional inclusion criteria: positive RT-PCR test and/or positive result in test for antibodies against the SARS-CoV-2 coronavirus 1–8 months prior to the study start. The exclusion criteria will consist of: absolute contraindications to exercise; unstable cardiac conditions; currently engaged in regular exercise training more than twice per week. The necessary minimum total number of participants (n = 84) was obtained using the G*Power program assuming detection of a moderate effect size of REPETITIONxGROUP interaction (d = 0.50 or eta square 0.06) for exercise capacity and fatigue with a significance level of 0.05 and statistical power of 0.85.

### 2.2. Randomization

Participants meeting the inclusion criteria will be randomized to one of 3 groups: water-based exercise, land-based exercise, or control (no exercise). The randomization sequence will be designed by an investigator external to the study using an Excel random number generator. Group allocation will be prepared in 5 random versions. Finally, the allocation providing the lowest F value for MANOVA comparing basic characteristics of the study subjects will be used. Randomization will be stratified according to age, sex, and the level of exercise capacity. Concealed allocation will be achieved using opaque envelopes. Due to the nature of exercise interventions, it will not be possible to blind the physiotherapist or participants. 

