### 2.5. Procedure

Participants will be recruited from Warsaw’s primary schools and primary healthcare units through various channels (flyers, e-mails, Facebook posts etc.) where information with a link and QR code to an online eligibility pre-screening questionnaire will be provided. The pre-screening will address the specific inclusion and exclusion criteria for the study, and basic demographic data. Concurrently, the eligible participants (children with parents) will be invited to undertake the main screening and diagnosis of a general practitioner at the Faculty of Rehabilitation, AWF Warsaw. The purpose of the study will be explained to the children and parents. After obtaining consent, the general practitioner will ensure all inclusion and no exclusion criteria have been met. Participants who meet the inclusion criteria will be invited to attend a baseline assessment at the Central Research Laboratory at AWF Warsaw. 

At the baseline assessment session, participants and parents will be requested to complete the PedsQL^TM^ 4.0 and CFSQ. The instructions will be explained by the principal researcher. In case of any doubt, parents and children will be able to ask the principal researcher for help. The research team will measure the participant’s weight and height and calculate body mass index (BMI). The general practitioner will perform an examination of the participants to determine any contraindications to exercise testing. Pulmonary function and exercise capacity testing will be performed. 

After completion of the baseline assessment, participants will be randomly assigned into one of three groups (water-based exercise, land-based exercise, or control), and simultaneous implementation of the two exercise programs will commence. The attendance rate will be recorded by the physiotherapists after each session. Children will also have attendance cards on which they will collect stamps to increase motivation to attend. After 8 weeks, all assessment measures for all participants will be repeated in the Central Research Laboratory at AWF Warsaw.

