### 2.6. Statistical Analysis

Normality of the distributions of the quantitative variables under study will be tested using the Shapiro–Wilk test. Data will be presented as mean ± SD where appropriate. The mixed-design ANOVA will be used to compare means. The interaction of fixed and repeated factors will be analyzed. Tukey’s post hoc test will be used for detailed comparisons. For variables that do not meet the criteria of normality of distribution, data will be presented as medians and quartile range. The Mann–Whitney U test will be used to compare the groups. The variables as well as their increments will be analyzed. Effect sizes will be assessed by partial eta squared (ANOVA) or the Glass rank-biserial correlation coefficient (the Mann–Whitney U test). The agreement of children’s and parents’ responses in the PedsQLTM 4.0 questionnaire will be analyzed with the compatibility factor Kappa-k. All statistical calculations will be conducted using the Statistica 14.0.0.15 program (TIBCO Software Inc., Palo Alto, CA, USA, 2020).

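### Allocation is restricted by stratification and a best-of-five pick, but the planned ANOVA ignores both, so its test is conservative wherever the balancing variables predict change

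*Protocol article*

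**What the plan says.** Section 2.2 (Randomization) of the protocol article describes four elements of the allocation:

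- Source: "The randomization sequence will be designed by an investigator external to the study using an Excel random number generator".
- Selection: "Group allocation will be prepared in 5 random versions", followed by "Finally, the allocation providing the lowest F value for MANOVA comparing basic characteristics of the study subjects will be used".
- Stratification: "Randomization will be stratified according to age, sex, and the level of exercise capacity".
- Concealment: "Concealed allocation will be achieved using opaque envelopes".

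The section does not name the characteristics that enter the MANOVA, say who runs it, or say whether the five versions are themselves stratified.

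Section 2.5 (Procedure) fixes the timing: "After completion of the baseline assessment, participants will be randomly assigned into one of three groups". Both exercise programs then start together, so a choice made on the whole roster is feasible.

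For the analysis, section 2.6 states: "The mixed-design ANOVA will be used to compare means". It names the interaction of the group and repeated factors, Tukey comparisons, and a Mann–Whitney test where normality fails. No stratification factor, balancing covariate or re-randomisation test is mentioned.

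**The concern.** An ordinary ANOVA judges the difference between groups against the spread that simple randomisation would produce. Stratification and the best-of-five pick both remove part of that spread, because they force the groups to be alike on chosen baseline variables. If those variables predict the outcome, the group means vary less from one possible allocation to another than the model believes. The variation explained by those variables still sits in the residual error. The p-value is then too large.

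The direction matters: the test rejects too rarely, and no false positives are created. What is at stake is sensitivity in a three-arm trial of 84 children, and a reported significance level that is not the one the test delivers. There is a secondary issue of reproducibility. With the MANOVA variables unnamed, different choices could select different lists, and a test that replays the allocation rule cannot be built without knowing the rule.

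**Working it through.** **Inputs from the protocol article.** Three groups, five candidate lists, and strata of age, sex and exercise capacity (section 2.2); N = 84 and significance level 0.05 (section 2.1); two time points (section 2.3).

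**Assumptions, because the article gives no figure.** 1:1:1 allocation (28 per group), normal data, pre-post correlation ρ of 0.5 or 0.7, and a MANOVA on age, sex and baseline capacity. There are 12 strata (3 ages × 2 sexes × capacity split at the median) with blocks of 3.

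**The plan's own figure.** The only stated figure nearby is N = 84. With the G*Power interaction form, λ = N·f²·m/(1 − ρ), f = 0.25 and m = 2, power at 84 is 0.820 for ρ = 0 and 0.861 for ρ = 0.1. The stated 0.85 therefore corresponds to ρ of about 0.07, which the article does not give; ρ = 0.5 would need only about 48. N = 84 is taken as given here, and nothing below depends on how it was derived.

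**Step 1: what the planned test is.** With two time points, the group-by-time F test is the one-way ANOVA F test on the change score, with 2 and 81 degrees of freedom.

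**Step 2: how far baseline predicts its own change.** With equal unit variances at both times, the covariance of baseline and change is ρ − 1 and the variance of change is 2(1 − ρ). So R² = (1 − ρ)²/[2(1 − ρ)] = (1 − ρ)/2, which is 0.25 at ρ = 0.5 and 0.15 at ρ = 0.7.

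**Step 3: a limit by hand.** If baseline capacity were balanced perfectly, the between-group mean square would shrink by about 1 − R² while the residual stayed put. For 2 and 81 degrees of freedom, P(F > x) = (1 + 2x/81)^(−40.5), so the 5% critical value is 40.5 × (20^(1/40.5) − 1) = 3.109.

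- ρ = 0.5: 3.109/0.75 = 4.146, and P(F > 4.146) = 0.019.
- ρ = 0.7: 3.109/0.85 = 3.658, and P(F > 3.658) = 0.030.

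These are approximate floors. Real balance is imperfect, so the true level lies between them and 0.05.

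**Step 4: simulation under the null** (12,000 trials per row, Monte Carlo error about 0.002):

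| Allocation | ρ | Planned ANOVA | Adjusted for the 3 variables | Model SE / true SE |
|---|---|---|---|---|
| One plain list | 0.5 | 0.050 | 0.052 | 0.267 / 0.265 |
| Best of five only | 0.5 | 0.029 | 0.048 | 0.267 / 0.249 |
| One stratified list | 0.5 | 0.027 | 0.050 | 0.267 / 0.244 |
| Stratified and best of five | 0.5 | 0.024 | 0.050 | 0.267 / 0.235 |
| Best of five only | 0.7 | 0.039 | 0.052 | 0.206 / 0.198 |
| One stratified list | 0.7 | 0.038 | 0.054 | 0.207 / 0.201 |

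Bias in the group difference was about zero in every row. A separate simulation at ρ = 0.7 gave 0.033 to 0.040. With three generic covariates that did not predict change, the level was 0.054, which is nominal within simulation error.

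**Step 5: what each restriction contributes at ρ = 0.5.** The two together move the level by 0.050 − 0.024 = 0.026. Stratification alone moves it by 0.050 − 0.027 = 0.023, and the pick alone by 0.050 − 0.029 = 0.021. The effects overlap: either alone gives most of the shift, and adding the pick to stratification takes the level only from 0.027 to 0.024.

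**Step 6: power.** For an assumed half-SD effect in both exercise arms under best of five (6,000 runs), power was 0.44 unadjusted and 0.58 adjusted at ρ = 0.5, and 0.69 and 0.76 at ρ = 0.7. Most of that gap comes from leaving the covariates out, not from the selection itself.

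**The case against.** Several stronger readings are tempting, and the article does not support them.

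- **That the pick contradicts stratification.** Five stratified lists can be generated and compared. The article leaves the combination unexplained, but it is not contradictory.
- **That concealment is breached.** Children are consented and tested at baseline before assignment, and the sequence comes from someone outside the study. The MANOVA F is also unchanged when arm labels are swapped, so the criterion cannot itself favour an arm. What remains is narrower: whoever runs the MANOVA handles children, baseline data and groupings together, and that person is not named.
- **That the p-values are wrong in a way that threatens a positive result.** The error is conservative and the estimates are unbiased. Nor does the pick always cost power against simple randomisation: near the planned power, a simulation with covariates explaining 25% of the change gave 0.887 with the pick and 0.865 with one plain list. The loss is relative to an adjusted analysis.
- **That reported confidence intervals are too wide.** Section 2.6 plans none, so the point concerns tests.

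Two further objections stand in part. The size depends on an unstated correlation and on baseline capacity being balanced. For fatigue, the other primary outcome, baseline CFSQ is not a named stratifier, and nothing shows that age, sex or capacity predict its change. It is also fair that an article may leave the MANOVA variable list and the model covariates to a fuller document, so their absence alone is not the finding. The article does, however, state both the restriction and the analysis, and as stated they do not match.

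**Conclusion.** The point holds as a mismatch between a doubly restricted allocation and an analysis that takes no account of it. For exercise capacity, the planned test runs at about 0.02 to 0.03 instead of 0.05 if the pre-post correlation is 0.5, and at about 0.03 to 0.04 if it is 0.7. This assumes 84 children, equal groups and baseline capacity among the balanced variables. For an outcome unrelated to the balancing variables there is no effect.

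A reader might infer that the best-of-five pick is the culprit and that deleting it cures the problem. It does not: one stratified list analysed without its strata gives nearly the same level. Because the error is conservative, creates no bias and is removed by a model change, this is a should-fix point, not a must-fix.

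**What to change.** 1. **Analysis (section 2.6).** Include age, sex, baseline exercise capacity and every variable used in the MANOVA pick as covariates in the primary model, for example an ANCOVA on the post-intervention value. Alternatively, use a re-randomisation test that repeats the stratified best-of-five rule. In the simulations above, adjustment brought the level back to 0.048 to 0.054.
2. **Allocation (section 2.2).** Either replace the pick with one stratified blocked list, or keep it with its variables fixed before any baseline data are seen and have only the external investigator run it. State that the candidate lists are stratified and where the envelopes come in.

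**Cost.** A few sentences. The stratifiers are already measured at baseline, and the external investigator is already in the plan. Three covariates take the residual degrees of freedom from 81 to 78. Dropping the pick may leave slightly more chance imbalance on unstratified variables, which adjustment can handle. If allocation has already been made, the first change is still available, provided that it is fixed before outcome data are examined and that the variables and rule actually used are on record.

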### 2.3. Outcome Measures

Outcome measures will be collected at baseline and immediately after the 8-week intervention. Table 1 shows the distribution of the different measures across the time points during the study (SPIRIT table).

#### 2.3.1. Demographic Data

Demographic data that will be collected include: age, sex, date of COVID-19 onset, current physical activity level (participation in organized physical activity per week), swimming skills, and symptoms of post-COVID-19 condition. Height and weight will be measured before and after the intervention.

#### 2.3.2. Diagnosis of General Practitioner

Participants will be required to undertake a pre-participation screening for exercise testing and training with the general practitioner including: a medical history questionnaire, general health screen, blood pressure, medication use, nutritional assessment, heat- and hydration-related risk factors, mental health considerations, tests for SARS-CoV-2 antibody only for participants without positive RT-PCR test and/or positive result in test for antibodies against the SARS-CoV-2 coronavirus in the 1–8 months prior to the study start.

